## Abstract

**Background:**

Medical professionals are at high risk of job stress and burnout. Research shows that work-related stress can be reduced through enhancing psychological resources, in particular, self-efficacy and perceived social support. These psychological resources can operate either individually or sequentially: in line with the cultivation hypothesis, self-efficacy precedes and cultivates perceived social support, whereas according to the enabling hypothesis it is perceived social support that comes first and enables self-efficacy. Based on this theoretical framework we developed an internet-based intervention, Med-Stress, dedicated to healthcare providers and aimed at reducing job stress and burnout. Med-Stress contains two modules that enhance self-efficacy and perceived social support, which are tested in four variants reflected in four study conditions. We expect that sequential enhancement of resources: self-efficacy and social support or social support and self-efficacy will yield larger posttest results than individual enhancement.

**Methods:**

In this four-arm randomized controlled trial we will test four variants of the Med-Stress intervention. The trial is open for professionally active medical providers aged at least 18 years (*N* = 1200) with access to an Internet-connected device. We will compare the effects of two experimental conditions reflecting cultivation and enabling effects of self-efficacy and perceived social support (sequential enhancement of resources), and two active controls strengthening self-efficacy or perceived social support. Job stress and job burnout will be the primary outcomes, whereas depression, job-related traumatic stress, and work engagement will be secondary ones. Additionally, we will measure perceived social support, self-efficacy to manage job stress and burnout, and the ability to obtain social support, exposure to traumatic events, and users’ expectancy and credibility of the intervention. All assessments will be applied before the intervention, at posttest (at 3 or 6 weeks depending on the study condition), and at 6-month and 12-month follow up. In the case of experimental groups, additional measurements will be taken after enhancing each resource.

**Discussion:**

Resource-based interventions are relatively context-free and could potentially benefit medical professionals across the field. If Med-Stress is successful, its most effective variant could be implemented in the healthcare system as a standalone, supportive tool for employees.

**Trial registration:**

ClinicalTrials.gov, NCT03475290 Registered on 23 March 2018.

**Electronic supplementary material:**

The online version of this article (10.1186/s13063-019-3401-9) contains supplementary material, which is available to authorized users.

## Background

A demanding work environment can detrimentally affect employees’ mental health, leading to job stress and burnout [1]. Job stress is a response to employees’ perceptions that their work demands exceed their ability to cope [2]. When this becomes a chronic state or is not adequately coped with, job stress can adversely affect employees, organizations and societies [3]. Concurrently, over the past four decades, the focus of occupational psychology has expanded to include job burnout as an indicator of mental health at work. Originally defined as a syndrome comprising emotional exhaustion, depersonalization, and decreased personal accomplishment [4], nowadays the popular view is that only the first two dimensions are required to recognize and measure job burnout [5]. Burned-out employees suffer from numerous physical and psychological conditions [6], commit more errors at work [7], and can “infect” others with their burnout [8]. Although job stress and burnout are rooted in the work environment, they can spill over into other life domains [9]. Estimating the prevalence of job stress and burnout is difficult and few countries recognize job burnout as a legitimate medical diagnosis (with some exceptions such as the Swedish version of International Classification of Diseases (ICD)-10 [10]). Thus, the distinction between job burnout and conditions with similar symptoms like fatigue, depression, and anxiety is often difficult to make [11], and can lead to classifying job burnout as another condition. Regardless of the specific diagnosis, the burden of job-related mental health problems among all professions involves direct costs of treatment but also indirect ones resulting from sick leave absences, job turnover, and early retirement, among others [12], making it a matter of public interest.

Although today we know that job stress and burnout are not limited to the helping professions, healthcare providers are still considered a vulnerable group [13]. This is particularly significant from the public standpoint because most of us become patients at some point in our lives. We surveyed 744 health workers in a pre-implementation study and found that 70% of the responders had experienced stress-related emotional and health problems themselves or observed them in their colleagues, while 60% declared that the symptoms of job burnout had become ubiquitous in their work environments. Moreover, 90% of the responders lacked institutional support in preventing stress and burnout ([name], [name], [name], [name]: Internet-based intervention for occupational stress among medical professionals: preimplementation study, unpublished report). These findings are in line with a recent systematic review on job burnout among physicians, which reported a prevalence of up to 80.5% [14], and with the 6th European Working Conditions Survey, which found that the health sector scored the highest on the so-called work intensity index comprising five types of job demands [1]. Studies conducted in various parts of the world [15, 16] confirm that stress and burnout are vital problems for medical professionals across the world, regardless of economic, system, and cultural differences. There is thus a pressing need for effective and widespread workplace interventions that meet the needs of this occupational group.

Over the past 25 years, there has been a rise in Internet-based mental health interventions that are delivered via new technologies (e.g., Internet, mobile apps, virtual reality). Occupational Internet-based interventions follow those dedicated to treating clinical conditions such as depression, anxiety, and phobias [17, 18]. They usually adopt the cognitive-behavioral therapy (CBT) framework and select general mental health conditions as outcomes; usually stress, depression, and anxiety [19]. We argue, however, that workplace interventions need to be derived from theoretical models developed to explain and predict work-specific conditions. For instance, interventions dedicated to targeting contextual factors at work could employ an influential job demands-resources model [5], whereas those focused on individual characteristics might adopt conservation of resources theory [20, 21]. Additionally, the outcomes should be representative of the work environment, such as job burnout or work engagement, rather than depression and anxiety, which tend to span all life domains. These issues have largely remained unaddressed, although there are notable exceptions (e.g., [22]). Evidence suggests that occupational Internet-based interventions do work. A few trials have succeeded in reducing job burnout [22–25], and results of meta-analyses demonstrate that they are successful in enhancing psychological well-being and increasing work effectiveness [26], and in reducing mental health problems such as stress and depression [19]. Work engagement, a positive counterpart of job burnout, reflecting vigor, absorption, and dedication to work [27], has been targeted less often [22, 25]. All the above listed outcomes are applicable in the occupational context, regardless of the demands of a given profession. However, healthcare providers experience unique demands such as indirect traumatic exposure (e.g., caring for trauma survivors) that can result in job-related traumatic stress. Although numerous Internet-based interventions address consequences of traumatic exposure in populations such as veterans (e.g., [28]), few of these focus on employees [24, 29].

Workplace interventions usually take into account the specific environmental factors, which maximizes the fit with their receivers’ needs but makes them difficult or impossible to generalize. An alternative is intervention targeting individual and social resources. The obvious downside of such interventions is that they do not match the needs exactly, but on the upside, have a greater chance of being relevant to many employees across a variety of workplaces. In other words, resource-based interventions can be beneficial for more employees, but might not address all their issues. According to conservation of resources theory [20], resources are “those objects, personal characteristics, conditions, or energies that are valued in their own rights, or that are valued because they act as conduits to the achievement or protection of valued resources” (p. 339). In this study we will consider two psychological resources, self-efficacy and perceived social support, the conduits to prevent and manage job stress and burnout, as well as expect their role in increasing work engagement, and decreasing depression and job-related traumatic stress.

Self-efficacy, a crucial concept in social cognitive theory [30], determines how people feel, think, and behave, and reflects their belief in being able to perform competently and achieve set goals despite obstacles. It allows the prediction of how employees will cope with work stress [31] and was found to have a medium, negative relationship with job burnout [32]. Apart from general self-efficacy, we distinguish context- or domain-specific self-efficacy, which is considered better at explaining and predicting outcomes [33]. As the primary outcomes in this study are job stress and burnout, we are interested in self-efficacy to cope with those. Additionally, as we explain later in this paper, we focus on the relationship between self-efficacy and perceived social support, and thus introduce self-efficacy to obtain social support.

Due to numerous definitions of social support, it now operates as an umbrella term, and authors of each study are expected to be precise in presenting their understanding of the concept. Our focus is on perceived social support, which we define as a reflection of the belief that help will be available when needed [34]. Compared with the support that is actually received, it is less dependent on environmental factors and more stable over time [35], which makes it a uniquely suitable part of the intervention that is based on enhancing individual resources, regardless of specific workplace context. Social support was found to play a number of roles in the process of job stress, from changing the perception of demands to moderating the strain-stress relationship [36], and a small negative relationship was found between perceived social support and job burnout [21].

Enhancement of perceived social support and self-efficacy was the focus of a previous intervention, Helpers’ Stress [25, 29], which was dedicated to professionals who worked with trauma survivors, and was found to be successful in reducing their job burnout and increasing work engagement. However, less is known about the joint impact of self-efficacy and perceived social support on mental health indicators. According to one of the predictions, the cultivation hypothesis, self-efficacy is a resource that comes first as it allows for reaching out to other people to obtain support when needed [37]. On the other hand, the enabling hypothesis proposes that that it is the perception of support availability or directly receiving help that enhances the sense of self-efficacy [38]. Both arguments have found considerable empirical support, however, mainly in the context of health behavior change [39], stress recovery [40], and work engagement [41]. What is lacking is experimental evidence from research conducted in an occupational setting and we aim to address this gap.

To summarize, the goal of this study is to test the efficacy of an internet-based intervention, Med-Stress, targeted mainly at reducing job stress and burnout among medical professionals, through the individual and sequential enhancement of self-efficacy and perceived social support. Med-Stress comprises two main modules - one dedicated to self-efficacy, and the other to perceived social support - that are then tested in four configurations that translate into four study conditions. Both modules are included in two of these conditions, which means that the resources are strengthened sequentially: in the first variant, a self-efficacy enhancement module precedes a perceived social support enhancement module, whereas in the second variant the order is reversed. Throughout the protocol we refer to these study conditions as experimental ones. Only one module is included in the remaining two conditions, which means that a single resource is targeted; either self-efficacy or perceived social support. These conditions are referred to as active controls. We expect that participation in all conditions will lead to significant changes in primary and secondary outcomes from the baseline to posttest. However, a greater decrease in job stress and job burnout (primary outcomes), depression, and traumatic stress symptoms, and greater increase in work engagement (secondary outcomes) at the posttest will be observed among the participants in the experimental conditions than among those in active control conditions. These differences will be maintained at the 6-month and 12-month follow up.

At the same time, we see no theoretical or empirical grounds to predict which of the two experimental conditions will be more effective than the other in reducing stress and burnout, and thus we consider a comparison between cultivation and enabling effects an explorative part of the study (see Figs. 1 and 2).

**Fig. 1 Fig1:**
[figure not shown]
Cultivation hypothesis

**Fig. 2 Fig2:**
[figure not shown]
Enabling hypothesis

Moreover, we make predictions on the mechanisms behind the impact of the study condition assignment on the primary and secondary outcomes. We hypothesize that self-efficacy and perceived social support will mediate - either individually or sequentially - the relationship between condition assignment and the outcomes: the impact of condition assignment on the primary and secondary outcomes posttest will be mediated by (1) self-efficacy or (2) perceived social support, or (3) sequentially by either self-efficacy and perceived social support or perceived social support and self-efficacy. The increase in self-efficacy and perceived social support will lead to a decrease in job stress and job burnout and in depression and secondary traumatic stress symptoms, and to an increase in work engagement posttest.

## Methods

### Design

We will conduct a four-arm randomized controlled trial in parallel design, comparing the effects of (1) self-efficacy and perceived social support sequential enhancement (experimental condition reflecting cultivation hypothesis), (2) perceived social support and self-efficacy sequential enhancement (experimental condition reflecting enabling hypothesis), (3) self-efficacy, and (4) perceived social support enhancement (active controls).

The study has been approved by a research ethics committee and registered at ClinicalTrials.gov on 23 March 2018 (study identifier NCT03475290). The registration process (including obtaining informed consent) and the entire study will be conducted online at medstres.pl.

### Study population

The study is aimed at medical professionals such as physicians, nurses, midwives, physical therapists, and paramedics. Participants will be required to meet the following inclusion criteria: (1) be at least 18 years old and (2) be pursuing an occupation related to health care. Lack of access to a device with an Internet connection will be an exclusion criterion. In line with national surveys, 84.2% of households and 95.6% of private and public entities in Poland have access to the Internet and mobile Internet devices are in common use [42]. However, 11% of medical professionals who participated in our pre-implementation study declared a lack of Internet connection at the workplace. Thus, this criterion has been set as a point for consideration for those potential participants who would be interested in using Med-Stress during working hours only. Participants do not need to meet any criteria for job stress or burnout levels.

### Sample size

The study will be conducted among professionally active health professionals at risk of job stress and burnout. Bonferroni’s adjustment for multiple comparisons will be applied: there will be a comparison between the two experimental conditions and between each experimental condition and each active control condition giving a total of five comparisons posttest. Furthermore, we will include five outcomes. Taken together, this will lower *p* levels to .002. Meta-analyses of the effectiveness of web-based interventions for stress reduction found a small effect of *g* = 0.30 [19] for work-related stress, and a medium size effect of *d* = 0.49 for general stress [43]. Taking into account the minimum effect size of *d* = 0.20, in analysis of covariance (ANCOVA) with a significance level of α = 0.002, statistical power of 0.90, and the number of conditions (two experimental conditions and two active controls), a total of 607 participants will be set (152 participants per condition). Furthermore, a high dropout rate is usually encountered in unguided interventions (between 5 and 45%; [44]) and thus we ultimately plan for a sample of 1200 participants (300 participants per condition).

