### Statistical analysis

We will conduct analyses of covariance (ANCOVA) with condition assignment as a factor, all primary and secondary measures at posttest as outcomes, and their pretest values as covariates. This will allow us to test for group differences between study conditions posttest while controlling for change over time. ANCOVA has been shown to be more parsimonious than analysis of variance (ANOVA) in randomized trials with a repeated measures design, and thus to have more power [56]. In terms of specific analyses, primarily, we will compare the effects of experimental conditions to each active control to test whether a two-module intervention is more effective that a single-module one. Next, we will compare the effects of the two experimental conditions to check if the sequence of the modules contributes to the intervention effects. Bonferroni’s adjustment for multiple comparisons (five comparisons and five outcomes) will be applied, which will lower the *p* levels to .002 for detection of the effects. Additionally, we will conduct separate ANCOVA to test whether the differences in outcomes between study conditions are maintained at the 6-month and 12-month follow up. Furthermore, we will conduct mediation analyses to verify the hypothesized mechanism of the effect of condition assignment on the primary and secondary outcomes. Sequential mediation analyses will be applied using the PROCESS macro [57] with condition assignment as a predictor, primary and secondary measures posttest as the outcomes, their baseline scores as covariates, and self-efficacy and perceived social support posttest as mediators (see Figs. 1 and 2 for conceptual models of mediations).

Additionally, we will carry out moderation analysis to test whether the initial (pre-intervention) expectancy about the positive outcomes of the treatment (i.e., how successful the intervention would be in reducing stress and burnout symptoms in participants’ opinions) moderates the relationship between the condition assignment and the study outcomes. As participants in the study will have the option of engaging in one or more out of four additional modules, we will consider participation in them as a control variable.

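### The 607 participants give 90% power for Cohen's f = 0.20 in a four-group omnibus test, not for the stated d = 0.20, and the planned pairwise tests have far less power at d = 0.20 unless the pretest correlation is very high

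*Protocol article*

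**What the plan says.** The Sample size section of the protocol article cites two meta-analytic effects, g = 0.30 for work-related stress and d = 0.49 for general stress. It then sets its own value: "Taking into account the minimum effect size of *d* = 0.20". The calculation is placed "in analysis of covariance (ANCOVA) with a significance level of α = 0.002", with "statistical power of 0.90, and the number of conditions (two experimental conditions and two active controls"). The result is "a total of 607 participants will be set (152 participants per condition"). Citing dropout of 5 to 45%, the section raises the target to 1200, or 300 per condition.

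The alpha comes from pairwise testing. The same section says "there will be a comparison between the two experimental conditions and between each experimental condition and each active control condition", which makes five comparisons; with five outcomes, 0.05/25 = 0.002. The Statistical analysis section confirms the use of these tests: "we will compare the effects of experimental conditions to each active control to test whether a two-module intervention is more effective". It enters each outcome's pretest value as the covariate. Neither section states a pretest-posttest correlation or whether tests are one- or two-sided.

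**The concern.** Two things do not fit together. First, the 0.20 follows directly on g = 0.30 and d = 0.49, so it reads as a cautious value on the same standardised-mean-difference scale. A test of d = 0.20 at alpha 0.002 with 90% power would normally need far more than 152 per arm. Second, the number of conditions is an input to the calculation, which suggests an omnibus test across four groups, whereas the alpha was derived for single pairwise contrasts and will be applied to them.

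The claimed power is at stake. If the 0.20 was entered as Cohen's f, the design was sized for a difference twice as large as the one named (in the two-versus-two pattern). That difference, d = 0.40, exceeds the g = 0.30 cited for work-related stress, so the apparent caution is reversed. The comparators are active single-module arms, so small differences are plausible. Someone who takes the paragraph at face value could read a null result as evidence against d = 0.20.

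**Working it through.** **Inputs.** From Sample size: effect 0.20, alpha 0.002, power 0.90, 4 groups, N = 607 (152 per arm), target 1200 (300 per arm), dropout 5 to 45%. From Randomization and blinding: 1:1:1:1 allocation. Assumed here: two-sided tests, and pretest-posttest correlation r = 0, 0.5, 0.7 or 0.8.

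**Step 1: reproduce 607.** For an ANCOVA F test with numerator df 3, denominator df N − 4 − 1 and noncentrality f²N, take f = 0.20 and alpha 0.002.
- N = 606: power 0.8995.
- N = 607: noncentrality 0.04 × 607 = 24.28, power 0.9002.

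So 607 is the smallest N that reaches 0.90, an exact match. It arises with no variance reduction from the covariate. The same f with numerator df 1 gives 483, so the match is specific to the 3-df test.

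**Step 2: use d = 0.20 as stated.** If both two-module arms differ by d from both one-module arms, the group means lie d/2 either side of the grand mean. Then f = d/2, so d = 0.20 is f = 0.10 and f = 0.20 is d = 0.40.
- With f = 0.10 the 3-df test needs N = 2405.
- At N = 607 its power is 0.14.

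Other patterns convert differently. With one arm high, one low and two midway, f = d/√8, so f = 0.20 is a largest pairwise difference of 0.20 × 2.83 = 0.57.

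**Step 3: power of the planned pairwise tests.** Use a noncentral t with df = 2n − 3, two-sided alpha 0.002 and noncentrality d√(n/2)/√(1 − r²). For example, d = 0.20, n = 152 and r = 0 give 0.20 × √76 = 1.74 against a critical value of about 3.1, hence power 0.087. At 45% dropout, 300 × 0.55 = 165 per arm remain.

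| Analysed per arm | d | r = 0 | r = 0.5 | r = 0.7 | r = 0.8 |
|---|---|---|---|---|---|
| 152 | 0.20 | 9% | 14% | 25% | 42% |
| 165 | 0.20 | 10% | 16% | 29% | 47% |
| 300 | 0.20 | 26% | 39% | 63% | 84% |
| 152 | 0.30 | 31% | 46% | 71% | 89% |
| 300 | 0.30 | 72% | 87% | 98% | >99% |
| 152 | 0.40 | 64% | 82% | 96% | >99% |
| 300 | 0.40 | 96% | 99% | >99% | >99% |

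Reading the tests as one-sided at 0.002 gives 13% to 33% for d = 0.20, n = 152 and r = 0 to 0.7.

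**Step 4: what would restore 90% at d = 0.20.** In the normal approximation, the pairwise test needs 1 − r² = n d²/[2(3.090 + 1.282)²].
- n = 152: 6.08/38.2 = 0.159, so r ≈ 0.92.
- n = 300: 12/38.2 = 0.314, so r ≈ 0.83.

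For the omnibus test in the two-versus-two pattern, r must be about 0.87 at 607 and 0.71 at 1200.

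**Step 5: pairwise d detectable with 90% power.** Solving step 3 for d at r = 0 / 0.5 / 0.7:
- 152 per arm: 0.51 / 0.44 / 0.36.
- 300 per arm: 0.36 / 0.31 / 0.26.

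**The case against.** The best defence is that the trial does not plan to analyse 152 per arm. It recruits 300, and the pretest covariate raises power, so the r = 0 column is not the planned analysis. That stands as far as it goes. A reader might infer that power at d = 0.20 is simply 9 to 25%, but that range holds only for 152 analysed per arm and r between 0 and 0.7, and the protocol fixes neither. A reader might also infer that 1200 cannot restore the claim at all. That is too strong: with every participant analysed, 90% is reached at r of about 0.83 for the pairwise tests and about 0.71 for the omnibus test.

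The defence does not rescue the paragraph, because 607 is what it claims gives 90%, and 1200 is justified there by dropout. At the upper dropout figure, 165 per arm remain, and power at d = 0.20 stays below 50% even at r = 0.8.

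Two further limits are fair. Against g = 0.30 the design is much less weak: with 300 per arm, power is 72%, 87% or 98% for r = 0, 0.5 or 0.7. That assumes no dropout, and the protocol does not present g = 0.30 as a difference between two-module and one-module arms. Also, the protocol nowhere says that a null result will be taken to exclude d = 0.20; that is a risk of misreading, not a stated plan.

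Could 0.20 have been meant as f? The calculation fits f, but the text writes d and places it beside two standardised mean differences, so the label is wrong even on that account.

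**Conclusion.** The paragraph is wrong as written. The total of 607 corresponds to f = 0.20 in a 3-df omnibus test, or d = 0.40 in the two-versus-two pattern, and not to d = 0.20. That 0.20 was entered as f is inferred from the exact match, since the protocol does not show the calculation. That d = 0.20 does not give 607 holds either way, unless an unstated correlation of about 0.87 (omnibus) or 0.92 (pairwise) is supposed.

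A second mismatch adds to the first: the sizing is for an omnibus test, whereas the alpha and the hypotheses concern pairwise contrasts. Even at d = 0.40, 152 per arm gives the pairwise tests 64% power at r = 0 and 82% at r = 0.5.

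The pairwise figures rest on two-sided testing, equal arms and assumed correlations. The f-to-d conversion rests on the two-versus-two pattern of means, which matches the trial's main hypothesis. The finding concerns the stated power. It does not show that 1200 is an unsuitable sample for the effects the trial may in fact produce.

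**What to change.** Keep the target of 1200 and restate the Sample size paragraph:

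- Replace the d = 0.20 label with the effect that gives 607: f = 0.20 in the four-group omnibus test, equal to d = 0.40 when both two-module arms differ equally from both one-module arms. Keep that condition in the wording.
- State a pretest-posttest correlation and its source. Under it, give pairwise power at alpha 0.002 for d = 0.20, 0.30 and 0.40 over 152 to 300 analysed per arm.
- State the pairwise difference detectable with 90% power across that range, and interpret null findings against the value for the number actually analysed.

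If d = 0.20 is truly the smallest difference of interest, the alternative is to recompute N for the pairwise contrasts. With the noncentral t this needs 959, 720, 490 or 347 analysed per arm for r = 0, 0.5, 0.7 or 0.8, before dropout.

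The restatement costs one paragraph and no extra participants. Its downside is a less favourable power statement.
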